### Relevant concomitant care permitted or prohibited during the trial {11d}

Physiotherapy will be given to the patient after implantation to restore mobility and muscle formation as part of the study protocol. Patients need to follow a rehabilitation programme to ensure proper reintegration into daily activities, work and sports and leisure. This process has to be accompanied by physiotherapists. Physiotherapy is considered to have a significant impact on the patients’ recovery process.

The main aims of the programme will focus on pain reduction, muscle strengthening (knee and hip muscles), proprioceptive training/stabilisation, optimising neuromuscular function and patient education. Rehabilitation programmes for both arms will aim at being as similar as feasible, both in regimes applied and in measures for adherence. However, during the initial phase (12 weeks), the therapy will differ as follows:

#### Experimental group (N-TEC)

The rehabilitation programme is designed to protect the implanted graft during the early postoperative phase. Protective measures include partial weight bearing with crutches for 6 weeks and restricted knee motion for 12 weeks following surgery.

#### Control group (PRP)

The primary objective is to prevent excessive loading of the painful knee joint. Therefore, therapeutic exercises involving knee movements against maximal resistance during extension and flexion, as well as those incorporating rotational components or performed in high-stress positions, such as kneeling, are not recommended. Additionally, physiotherapy is not advised within the first 3 days following injection.

### Provisions for post-trial care {30}

Moreover, this treatment is not a ‘point of no return’ as it leaves open the options to perform all other treatments available.

### Outcomes {12}

#### Primary outcome

The primary outcome is the change in KOOS Pain subscale from baseline (day 0 or up to 1 month before) to 24-month follow-up visit and it will be assessed by the KOOS questionnaire.^26^ The KOOS questionnaire is a patient-reported outcome measure (PROM) questionnaire with five different subscales (pain, symptoms, activity of daily living, sports activities and quality of life (QoL).^26^ The KOOS Pain subscale demonstrates a high intraclass correlation coefficient (ICC) ranging from 0.80 to 0.97 in individuals with OA, indicating excellent reliability.^27^ The questionnaire is filled in online by a patient up to 2 weeks before the follow-up visit online. In exceptional cases, when the patient did not fill in the questionnaire before the visit online, this can be done in the clinic before the visit. The score is automatically calculated by the database according to the equation defined in the questionnaire.

#### Secondary outcomes

##### Questionnaires

The PROMs have been selected to address the core domains (pain, physical function patient global assessment and joint integrity) of patient-reported outcomes and based on their reliability and validity as well as their wide use in the clinic.^2628^,^32^

All questionnaires are completed online by the participants at baseline, after 6, 12 and 24 months.

KOOS: in addition to the KOOS Pain subscale, we will evaluate the mean KOOS subscores at all timepoints (baseline, 6, 12 and 24 months). These data will give an indication of the recovery of the patient over time and potential differences between the two groups at defined time points.^26 27^Kujala Anterior Knee Pain Scale: this questionnaire is specifically designed and therefore, especially suited for patellofemoral pain. The results will allow a comparison between groups as well as verification of the results from the KOOS scores.^28^Western Ontario and McMaster Universities Osteoarthritis Index (WOMAC): the WOMAC was chosen as it is broadly used in the literature for OA and will allow comparison of results with external references.^27 29^European Quality of Life-5 Dimensions (EQ-5D-5L): this questionnaire is used to assess overall changes in patients’ QoL.^30 32^ The widely used questionnaire is especially important for health economic assessments and comparison with the literature data.Global Rating of Change: this widely used score assesses whether the patient condition has gotten worse, better or stayed the same and to quantify the magnitude of that change.Marx Activity Rating Scale: this activity-related PROM is widely used to assess the activity of a patient after treatments of the knee.^31^Visual analogue scale (VAS): the VAS is used to measure the pain of the patient.^33^

##### Non-responders

The number of non-responders was chosen as secondary outcome parameter because of the importance to assess how many patients will respond or not to the treatments. An improvement in KOOS Pain of 13 on a scale of 0–100 is considered a minimal clinically important difference; lower changes are typically associated with ‘non-responders’.^27^

##### Treatment failures

Treatment failure is defined as objective pathological clinical findings by the investigator directly correlated with subjective patients’ complaints resulting in a clinical deterioration of the subjective clinical outcome assessed by KOOS. Moreover, a patient is considered as treatment failure, when switching to an alternative surgical regenerative treatment or knee replacement. A clinical deterioration is defined as reduction in the KOOS score of >13 compared with baseline.

##### Radiological assessment

For the radiological evaluation of the OA knee joint, a comprehensive assessment of the whole joint with X-ray and MRI combining morphometric analysis, semiquantitative scoring and compositional measurements in several subregions of the knee joint is mandatory. MRI assessments were chosen as secondary outcome parameters as they allow monitoring of disease progress and assessment of maturation of the repair tissue. The latter is expected to provide an insight into the healing process and the possible regenerative nature of the treatment, to be correlated with mid-term and long-term clinical course of the disease. Moreover, MRI Osteoarthritis Knee Score (MOAKS) and MRI of Cartilage Repair Tissue (MOCART) scores provide an objective endpoint of high clinical relevance to assess cartilage regeneration, which is known not to be reached in the comparator group.^34^,^36^ Both MOCART and MOAKS scores have shown good inter-rater reliability and are widely used as standardised tools for assessing structural cartilage outcomes in clinical and research settings.^34 35^

The following parameters will be assessed

MOAKS for radiological evaluation of OA at 6, 12 and 24 months.MOCART for radiological evaluation of repair tissue at 6, 12 and 24 months.OA grade according to Iwano and Kellgren/Lawrence classification at baseline, 6, 12 and 24 months.

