**Methods and analysis:**

A randomised controlled trial involving 75 patients with patellofemoral osteoarthritis from nine different clinical centres in Switzerland, Germany and Croatia is being conducted to evaluate the effectiveness of N-TEC implantation compared with standard treatment with platelet-rich plasma (PRP). In the intervention group, an autologous nasal cartilage cell-derived graft is implanted into the cartilage defects of the patella and/or trochlea during an open surgical procedure. The control group receives three PRP injections at weekly intervals. The primary outcome is the mean Knee Injury and Osteoarthritis Outcome Score Pain Change from baseline to 24 months between groups. Secondary outcomes, including patients’ self-assessed questionnaires, X-ray and MRI scans, physiotherapeutic assessments and safety, will be assessed and compared between the intervention and control group. In addition, the study is complemented with a health-economic evaluation to establish the intervention’s value for money and impact on productivity in working-age individuals. The planned duration of the study is 4 years including baseline and follow-up measurements at 6, 12 and 24 months.

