#### Secondary objectives

Secondary objectives aim (1) to compare the development of the patients’ recovery over time between groups and (2) to determine the integration of the graft, the maturation of the repair tissue and the progression or remission of the disease. In addition, the regenerative potential of the treatment will be assessed by evaluating cartilage regeneration. Treatment failures are also of interest for the evaluation.

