### Participant timeline {13}

Table 1 provides an overview of the participant timeline, from the first visit to the last follow-up measurement, including all assessments that are conducted.

**Table 1 T1:** Participant timeline

Study periods	Screening	Treatment			Follow-up			
		N-TEC		Control (PRP)				
Visit	1	2a	2b	2	3	4	5	6
Time (hour, day, week, month)	≤ 6 m	Day −32	Day 0	Day 0, 7,14	6w	6m	12m	24m
Day	≤ 180	- 32	0	0, 7, 14	42	180	360	720
Acceptable time delay		0d	1d	2d	2w	4w	6w	8w
PIC	x							
Medical history	x							
Inclusion/exclusion criteria	x							
Laboratory tests (serology)	x	x						
Pregnancy test	x							
MRI*	x	(x)				x	x	x
X-ray*	x	(x)				x	x	x
Questionnaires†	x	(x)				x	x	x
EQ-5D-5L	x	(x)	x		x	x	x	x
Health economic data	x				x	x	x	x
Physiotherapy tests	x					x	x	x
Harvesting of nasal cartilage biopsy		x						
Surgery (implantation)			x					
PRP injection				x				
Clinical examination	x	x	x	x	x	x	x	x
Adverse events‡	x	x	x	x	x	x	x	x
Physiotherapy§			x	x	x	x		

* MRI and X-ray must be repeated if they were not performed during screening or were conducted more than 6 months before treatment (day 0).

† Questionnaires must be repeated if completed more than 1 month prior to treatment (day 0).

‡ Recording of the adverse events is a permanent process independent of specific visit.

§ Physiotherapy sessions will be performed continuously as prescribed by surgeon independent of specific visit. Physiotherapy is performed for 18 weeks (4.5 months) but can be prolonged if medically indicated.

EQ-5D-5L, European Quality of Life-5 Dimensions; N-TEC, nasal chondrocyte tissue-engineered cartilage; PIC, patient informed consent; PRP, platelet-rich plasma.

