## Assignment of interventions: blinding

### Who will be blinded {17a}

The study is not blinded as blinding of patients is not possible for ethical reasons (injection vs surgery). Also, assessors of MRI/X-ray cannot be blinded, as an experienced person will detect the implantation of the graft.

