## Data collection and management

### Plans for assessment and collection of outcomes {18a}

Study data will be captured via the online CDMS REDCap^®^, based at the IT Department of the University Hospital Basel. The questionnaire as a measure for the patient- reported outcomes will be included in the electronic CRF to be filled in by the patient before the visit or directly at the site online or on paper.

All investigators directly involved in the patients’ information about the study, study intervention and follow-up will have to provide the certificate of Good Clinical Practice (GCP) training and/or follow additional national and local requirements on investigator qualification.

All outcomes are evaluated at baseline, and at 6-month, 12-month and 24-month follow-ups. Furthermore, the EQ-5D-5L and health economic data will be collected at the clinical visit scheduled for 6 weeks post-intervention.

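### The protocol contradicts itself on baseline MOAKS, does not say in which arm MOCART is scored, and waives masked image reading more widely than its reason supports

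*Protocol article*

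**What the plan says.** All places are in the protocol article.

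- Radiological assessment lists "MOAKS for radiological evaluation of OA at 6, 12 and 24 months" and "MOCART for radiological evaluation of repair tissue at 6, 12 and 24 months". The third item in that list is "OA grade according to Iwano and Kellgren/Lawrence classification at baseline, 6, 12 and 24 months".
- Plans for assessment and collection of outcomes {18a} states: "All outcomes are evaluated at baseline, and at 6-month, 12-month and 24-month follow-ups".
- Participant timeline {13}, Table 1, schedules MRI at screening. Its footnote says "MRI and X-ray must be repeated if they were not performed during screening", or if they are more than six months old at day 0.
- Secondary objectives include determining "the progression or remission of the disease".
- The abstract says that secondary outcomes, including "X-ray and MRI scans, physiotherapeutic assessments and safety, will be assessed and compared between the intervention and control group". The Discussion likewise promises a comparison of structural outcomes between the treatments.
- Who will be blinded {17a} gives up masked image reading altogether: "Also, assessors of MRI/X-ray cannot be blinded, as an experienced person will detect the implantation of the graft".

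**The concern.** Three features of the imaging plan do not fit its purpose.

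1. **Baseline MOAKS.** Progression and remission are changes within a patient, so a follow-up score alone does not describe them. The outcome list omits baseline for the MRI score and includes it for the X-ray grades, so the omission can be read as deliberate. The general sentence in {18a} points the other way.
2. **MOCART.** It grades repair tissue. Control patients receive injections only, so the score has no evident object in that arm. The text nevertheless couples it with MOAKS as an endpoint for cartilage regeneration and promises between-arm imaging comparisons without naming the arm in which MOCART is scored.
3. **Masking.** The stated reason for unmasked reading is that the graft can be seen. The waiver covers every MRI and X-ray, including images taken before any graft exists.

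The overall aim includes verifying regenerative and disease-modifying properties, and these images are the main structural evidence for it. At stake are a defined measure of MRI change, the precision of the MOAKS comparison, and protection against detection bias, which the protocol itself lists among its limitations.

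**Working it through.** **Is baseline MOAKS planned?** The outcome list says 6, 12 and 24 months. Section {18a} says baseline as well. The general sentence does not settle the matter: taken literally, it would also require MOCART before any repair tissue exists, so it cannot hold word for word for every outcome. The outcome list names baseline where the X-ray grades need it. Both readings are open, and a reader of scans could follow either.

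**Is the image available?** Yes. Table 1 schedules a pre-treatment MRI for all patients, not more than six months before day 0. Only the scoring is in doubt.

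**What does follow-up-only analysis cost?** The protocol states no figure for MOAKS, so there is none to reproduce. Its sample size concerns KOOS Pain and is unaffected: 30 evaluable patients per arm, a difference of 15 and an SD of 17.2 give 92.2% power (normal approximation) or 91.3% (t distribution), and 60/(1 − 0.20) = 75.

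Inputs for the precision check:

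- Completers: 75 − 15 = 60, from Sample size {14}.
- r, the correlation of baseline with follow-up MOAKS: not given in the document. This is an assumption, shown over a range.

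For a linear model, the variance of the unadjusted comparison relative to the baseline-adjusted one is 1/(1 − r²). The number of adjusted patients giving the same precision as 60 unadjusted ones is 60 × (1 − r²).

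| r (assumed) | 1/(1 − r²) | 60 × (1 − r²) |
|---|---|---|
| 0.3 | 1/0.91 = 1.10 | 54.6 |
| 0.5 | 1/0.75 = 1.33 | 45.0 |
| 0.6 | 1/0.64 = 1.56 | 38.4 |
| 0.8 | 1/0.36 = 2.78 | 21.6 |

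The loss runs from slight to large depending on r. MOAKS is semiquantitative and scored by subregion, so a linear-model ratio is only a guide.

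**MOCART by arm.** The target is repair tissue. N-TEC patients have an implanted graft; PRP patients have three injections. Two parts of the secondary objective, graft integration and repair-tissue maturation, fit MOCART and concern the implanted arm only. The comparative part, progression or remission, can be carried by MOAKS and the X-ray grades in both arms.

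**Where the masking reason applies.**

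- Pre-treatment MRI and X-ray: no graft exists, so the reason cannot apply.
- Follow-up MRI: the protocol says an experienced reader will see the graft, and nothing in the document contradicts this.
- Follow-up X-ray: Intervention description {11a} describes a cell-seeded collagen membrane fixed with resorbable sutures. The document gives no reason why this would show on a plain film. The same section allows tibial tuberosity osteotomy and bone grafting in the N-TEC arm, which may show. The reason is therefore unsupported for films without such a procedure and plausible for films with one.

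**The case against.** The strongest reply is that this is a wording gap in a condensed article. Section {18a} supplies the baseline, the scan is scheduled, and the MOAKS line does not exclude a baseline read. Much of that stands, and it limits how far the point can be taken.

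- A reader might infer that the trial cannot show progression or remission. The documents do not support that. Iwano and Kellgren/Lawrence grades are listed at baseline and at every follow-up with no restriction to one arm, and {18a} can be read as covering MOAKS.
- A reader might infer that, without baseline MOAKS, chance differences in initial severity would bias the comparison. Randomisation keeps a follow-up-only comparison unbiased, and chance imbalance is reflected in the confidence interval. The loss is one of precision, and its size rests on a correlation that the document does not give.
- A reader might infer that a between-arm MOCART test is planned. None is stated; the abstract speaks of imaging in general. The fair criticism is only that the arm is not named.
- One might want tibiofemoral subregions made the between-arm progression measure. That is a preference, not the correction of an error. Remission would have to appear in the treated patellofemoral compartment.
- On masking, the open-label limitation is acknowledged, and concomitant procedures may reveal the arm on some films. That limits what masking can achieve, but it does not justify waiving it for pre-treatment images.

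What the reply does not remove is that two sections give different schedules for the same score, and that following the outcome list leaves a stated objective without a starting MRI value.

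**Conclusion.** The point holds as a contradiction to be reconciled, with two related clarifications. The outcome list and {18a} disagree on baseline MOAKS. If the list is followed, MOAKS change is not available, and the between-arm comparison, though unbiased, has a variance about 1.1 times (r = 0.3) to 2.8 times (r = 0.8) that of an adjusted analysis. These ratios assume a linear model and an r that the document does not supply. MOCART should be tied to the arm in which it has an object. The blinding waiver is wider than its own reason: it cannot apply to pre-treatment images and is unsupported for follow-up plain films that show no concomitant procedure.

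The outcomes concerned are secondary, and no figure in the sample size section changes. The correction is still worth making, because it serves a stated objective and uses images already scheduled.

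**What to change.** 1. In Radiological assessment, state that MOAKS is scored on the screening MRI (or its repeat) as well as at 6, 12 and 24 months, so that the list agrees with {18a}. Qualify the general sentence in {18a} so that it does not require a pre-treatment MOCART.
2. Analyse follow-up MOAKS adjusted for its baseline value, as the statistical methods section {20a} does for KOOS, with a model suited to a semiquantitative subregional score.
3. State that MOCART is descriptive within the N-TEC arm, and that the structural comparison promised in the abstract and Discussion rests on MOAKS and the X-ray grades.
4. Narrow the waiver in {17a}. The existing readers grade pre-treatment MRIs and X-rays, and follow-up X-rays on which no concomitant procedure is visible, with arm and identity removed and before they see the same patient's follow-up MRI.

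The cost is one extra MOAKS read per patient on an image already taken, plus de-identification and ordering of the reads. No extra scans or readers are needed. Masking will remain incomplete where an osteotomy or bone graft can be seen, and the report should say so.

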##### Safety outcomes (biovigilance)

The study will evaluate the safety of the implantation of N-TEC by the number of serious adverse drug reactions or Suspected Unexpected Serious Adverse Reactions from baseline assessment up to 24-month follow-up assessment. Adverse events/adverse drug reaction will be graded according to severity, expectedness and relationship to trial treatment and reported according to the regulations.

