#### Safety objectives

A further objective of the study is to examine the safety of implanting N-TEC.

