### Adverse event reporting and harms {22}

During the entire duration of the study (category C), all adverse events (AE) and all SAEs are collected, fully investigated and documented in source documents (patient’s records) and CRFs. Study duration encompasses the time from when the participant signs the informed consent until the last protocol-specific procedure has been completed and includes a safety follow-up period of up to 2 years.

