## Discussion

The aim of this study is to evaluate the use of N-TEC in comparison with PRP as a standard treatment option for patients with isolated PFOA. Safety, pain, function and structural outcomes of both treatments are compared. In addition, the study is complemented with a health-economic evaluation to establish the intervention’s value for money and impact on productivity in working age individuals.

Currently, no regenerative treatment options exist for PFOA. This study is the first RCT to evaluate the efficacy of N-TEC and the first to investigate a regenerative intervention in this condition. A previous study demonstrated promising results for N-TEC in the treatment of focal chondral lesions of the knee joint.^42^ Furthermore, its safety and feasibility were confirmed in case studies with OA^43^ as well as pilot patients treated under temporary authorisation in Switzerland suffering from PFOA (unpublished results).

A notable strength of this study is the combination of both subjective and objective outcome measures. In addition to PROMs, the study design includes objective criteria such as radiographic and MRI assessments, activity monitoring and standardised physiotherapeutic evaluations. Although postoperative physiotherapy is delivered at various locations, all participating physiotherapists receive individualised training in the standardised rehabilitation protocol. This ensures a uniform application of core treatment principles, while still allowing for patient-specific adaptations.

Nevertheless, the study has certain limitations. Due to the inclusion of a non-surgical comparator, blinding of participants is not possible, which may introduce bias. Also, a surgical approach may be seen by some patients as potentially having greater benefit, which may also introduce bias in the patient self-reported outcome.

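### The declared safety outcome counts only serious reactions attributed to treatment, and only for N-TEC, which does not match the between-arm safety comparison the article promises

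*Protocol article*

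**What the plan says.** The Protocol article describes safety in five places.

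- **Safety objectives:** "A further objective of the study is to examine the safety of implanting N-TEC". Only the experimental treatment is named.
- **Safety outcomes (biovigilance):** the measure is stated explicitly. N-TEC implantation is to be evaluated "by the number of serious adverse drug reactions or Suspected Unexpected Serious Adverse Reactions from baseline assessment up to 24-month follow-up assessment". A second sentence adds: "Adverse events/adverse drug reaction will be graded according to severity, expectedness and relationship to trial treatment and reported according to the regulations".
- **Abstract, Methods and analysis:** secondary outcomes including "physiotherapeutic assessments and safety, will be assessed and compared between the intervention and control group".
- **Discussion:** "Safety, pain, function and structural outcomes of both treatments are compared".
- **Adverse event reporting and harms {22}:** over the whole study, which runs from signed consent, "all adverse events (AE) and all SAEs are collected, fully investigated and documented". Table 1 ticks adverse events at every visit in both arms, including the biopsy, surgery and PRP visits, and its footnote makes recording continuous.

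**The concern.** The objective concerns a procedure. Under Intervention description {11a}, an N-TEC patient has a biopsy of the nasal septum and then surgery on the knee (open, according to the abstract). Ligament surgery, tibial tuberosity osteotomy or bone grafting may be added. The control patient has three injections. The extra harm to be weighed against any KOOS Pain benefit is therefore largely procedural.

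The declared outcome passes events through a causality filter before counting them. A serious complication put down to the operation or the biopsy is an SAE. In the ordinary sense of the term it need not be an adverse drug reaction. The trial is open (Who will be blinded {17a}) and the two treatments are very different, so attribution may work differently in the two arms. At stake is whether a low count of serious reactions is later read as evidence that the whole procedure is safe, or as the result of the promised comparison.

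**Working it through.** The article gives no design figure for safety. Its power statement concerns KOOS Pain and has no bearing here. The check is therefore mainly a reading of the sections against each other.

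**1. What the count contains.** A serious adverse drug reaction must be serious and suspected to be caused by treatment. A SUSAR is a serious reaction that is also unexpected, so it is already included in the first category. The second term adds no events. Serious events judged unrelated, and all non-serious events, are outside the count.

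**2. Which arms it covers.** Safety objectives and Safety outcomes name N-TEC only. The abstract and Discussion compare both arms. No stated safety measure covers PRP.

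**3. Whether another outcome fills the gap.** Treatment failure covers a KOOS fall of more than 13 points tied to clinical findings, or a switch to other regenerative surgery or knee replacement. Other re-operations are not counted there. Nor is a serious complication that resolves without such a fall.

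**4. When the window opens.** Baseline is not defined for safety, and Table 1 has no baseline column. The possible readings are:

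| Reading of baseline | Window opens | Biopsy at Day −32 (Table 1) |
|---|---|---|
| KOOS Pain definition in Outcomes {12} | at most 1 month (28 to 31 days) before day 0 | missed by 1 to 4 days |
| Screening visit in Table 1 | up to 180 days before | included |

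Intervention description {11a} gives the interval from biopsy to implantation as 4 weeks (28 days). On that figure the biopsy falls within 1 month even under the KOOS Pain definition.

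**5. Patients biopsied but not implanted.** Criteria for discontinuing {11b} lists contamination of the product and unsuccessful manufacture as reasons for exclusion from the study. Such patients have had the biopsy but no implantation, so a measure of implantation safety may leave them out.

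**6. Whether the data exist.** They do. Section {22} and Table 1 capture all adverse events and SAEs in both arms from consent. Visit 2a (the biopsy) exists only for N-TEC, so allocation precedes it. A window that opens at randomisation therefore always includes the biopsy.

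**7. Illustration of size (assumed rates, not from the documents).** 75 patients allocated 1:1 give about 37 or 38 per arm. Suppose 3 of 37 N-TEC patients have a serious operative complication: 3/37 = 8.1%. The all-cause outcome records 3. The declared outcome records between 0 and 3, depending on attribution.

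Even an all-cause comparison would be mainly descriptive. With arms of 38 and 37, two-sided Fisher exact power is about 0.13 for 10% against 1%, 0.61 for 20% against 2%, and 0.80 for 30% against 5%. An interval is therefore more useful than a test.

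**The case against.** The strongest reply is that nothing is lost. Every adverse event and SAE is collected whatever its cause, and the second sentence of the safety section has them graded and reported. By-arm tables are ordinarily left to the analysis plan, which is not shown. This stands against any claim about data collection. It does not answer the point that the article itself fixes the safety measure, and fixes it more narrowly than the comparison it promises. That is a stated rule, not a detail lost in condensing.

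Four stronger readings are tempting, and the documents do not support them.

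- **That the between-arm comparison cannot be made.** It can, from the data collected under {22} and Table 1.
- **That surgical harms are definitely excluded.** Causality is graded against the trial treatment, which could be read to include the implantation procedure. The article does not settle this. That sentence also governs grading, not the count.
- **That biopsy harms definitely fall before the window.** This borrows a baseline definition written for a questionnaire and turns on a few days. If baseline means screening, the biopsy is inside.
- **That a count of zero would appear to rule out a true rate of 8%.** The one-sided 95% upper bound for 0/37 is 1 − 0.05^(1/37) = 7.8%, but the two-sided limit is 1 − 0.025^(1/37) = 9.5%, which does not exclude 8%. A bound on attributed reactions also measures something different from a rate of all serious events, and the article plans no such bound.

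Naming SUSARs alongside serious reactions is redundant, but nothing suggests that events would be counted twice.

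**Conclusion.** The point holds as a defect in the outcome definition. The declared measure is filtered by causality, restricted to N-TEC and opened at an undefined baseline. It can therefore leave out serious surgical or biopsy complications that investigators do not attribute to treatment, and it does not match the comparison promised in the abstract and Discussion.

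The extent of any under-count cannot be computed from the documents. It depends on the true complication rate, on how relatedness to treatment is interpreted, and on which baseline is meant. The first of these is not given and the other two are not settled. Sample size, the primary analysis and data collection are unaffected. The outcome should be changed before results are known, because a low number of serious reactions could otherwise stand in for the safety of the whole procedure.

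**What to change.** Redefine the safety outcome as the number and proportion of patients with at least one SAE, regardless of causality, by randomised arm, from randomisation to 24 months. Report the risk difference with its 95% CI. In addition:

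- show biopsy-related and surgery-related events separately, including those in patients who were biopsied but not implanted;
- report serious reactions and SUSARs as a subset of the SAEs;
- replace the undefined baseline start with randomisation;
- reconcile Safety objectives and Safety outcomes with the abstract, {22} and the Discussion, so that all describe the same arms, events and period.

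The cost is revised wording and a few more tables. No new visits, data or patients are needed. The drawback for the sponsor is that the reported N-TEC event rate will probably look less favourable than a count of attributed serious reactions.
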